### Sample size calculation

With the current standard of care, about 30% of all women will proceed from 500 ml to 1000 ml of blood loss. With a reduction from 30% to 15% (beta 0.80, alpha 0.05), 2 × 118 (236) women will have to be included. We aim to include 250 women, to compensate for loss to follow up or incomplete data.

### Safety concerns

A data safety monitoring board has been established to perform ongoing safety surveillance and interim analyses of the safety data. The board will be informed in any case of a severe adverse event. The board is composed of three independent physicians: [name] (anesthetist), [name] (gynecologist from a hospital not involved in the trial), and Dr. [name] (epidemiologist). [name] is chairman of the board. Further details about the board are listed in a separate charter, which is available on request.

The data safety monitoring board will meet by teleconference after the first 2 × 25 patients have been treated and after every 50 patients thereafter per group, and will conduct an interim analysis on the primary objective measure and the composite measure of severe outcome events (maternal death, use of more than four units of packed cells, intensive care admittance, embolization, or operative intervention.) The formulas proposed by Prochan, Lan and Wittes [14] will be used for the interim analysis.

In the analysis conducted by the data safety monitoring board, a correction will be made for possible confounders for the primary outcome, such as risk factors for PPH and difference in combined severe outcome. Should there be a statistical significant difference in severe adverse events between the intervention and the control group that cannot be accounted to other factors, such as selection bias in small groups, the data safety monitoring board shall decide whether the study should be continued. The study could be terminated prematurely on the advice of the data safety monitoring board if one of the treatment protocols shows less progression to severe blood loss and less maternal morbidity; in this case, it is not ethically justified to continue the study. All communications by the data safety monitoring board are reported via email to HS and PS. The final decision to terminate the trial on the advice of the data safety monitoring board lies with HS.

The trial is overseen by PS and HS. They are responsible for all communications with participating hospitals and local research nurses, and are also responsible for communication with the data safety monitoring board, the ethics committee, and the trial registration bureau.

Insurance policies are available to patients in case of adverse outcomes with lasting effects due to the study intervention.

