### Randomization, procedures, and collection of data

In women with more than 500 ml blood loss and ongoing blood loss, randomization takes place. Treatment allocation is blinded by use of opaque and sealed envelopes. The randomization is stratified per center, in blocks of four and concealed, in an allocation of 1:1. The envelopes will be distributed per center by Maastricht University Medical Center. The required randomization envelopes will be quickly and easily accessible at the labor ward. Participants will be randomized to either the intervention group (receiving fluids at 0.75–1.0 times the blood loss) or the control group, who will receive care as usual (receiving fluids at 1.5–2.0× blood loss).

In women participating in the study, blood loss will be measured by weighing the absorption towels after childbirth, excluding the first one directly after giving birth, as this will include amniotic fluid. In current care, generous volume resuscitation is standard; this consists of about twice the lost volume and 2 l fast infusion in patients with unstable bleeding. Volume resuscitation will primarily be done with a fast infusion of crystalloids or Ringers lactate. In all women, the first 2000 ml will consist of a fast infusion of NaCl (0.9%) or Ringers lactate, or a combination of the two.

At the stage of 500–750 ml blood loss, the study protocol starts (*t*_1_). Intravenous access will be established and a blood sample taken for testing hemoglobin concentration, hematocrit, platelet count, activated partial thromboplastin time, prothrombin time, and fibrinogen concentration. Women delivering in the Maastricht University Medical Centre ROTEM® analysis (FIBTEM, APTEM, INTEM, EXTEM) will be included. Hemodynamic parameters include blood pressure and oxygen saturation, as measured using continuous pulse oximetry.

Additional clinical parameters will guide management and serve as a safety check. We aim to maintain systolic blood pressure > 90 mmHg and diastolic blood pressure > 50 mmHg, or a decrease of less than 20 mmHg. The maternal heart rate should be less than 125 beats per minute [13]. If these cut-off values are crossed, an additional volume of 500 ml will be administered in 15 min, in both groups.

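### The interim looks that can stop the trial for benefit are not carried into the sample size or a final level, and the board's adjusted interim analysis targets a different effect from the final one

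*Protocol article*

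**What the plan says.** Under Safety concerns, the board meets after 25 women per group and then after each further 50 per group. At these meetings it "will conduct an interim analysis on the primary objective measure and the composite measure of severe outcome events". Published formulas are cited for the interim analysis, and further details about the board are said to be in a separate charter. On stopping, the article says: "The study could be terminated prematurely on the advice of the data safety monitoring board if one of the treatment protocols shows less progression"; lower maternal morbidity is required as well. The same section adds: "In the analysis conducted by the data safety monitoring board, a correction will be made for possible confounders for the primary outcome". The examples given are risk factors for PPH and the difference in the combined severe outcome.

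Under Sample size calculation: "With a reduction from 30% to 15% (beta 0.80, alpha 0.05), 2 × 118 (236) women will have to be included". The 0.80 printed as beta is evidently the power. The target of 250 allows for loss to follow-up or incomplete data. Interim looks are not mentioned.

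Under Statistical analysis, the primary result is the between-group difference in proportions with a confidence interval. Regression is used only if important baseline variables differ greatly. No significance or confidence level is given.

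Trial status reports that an interim analysis took place in October 2017, that 179 of 250 women are enrolled, and that the trial may end if the board intervenes after a planned interim analysis.

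**The concern.** Two things that the article states do not fit together.

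First, the trial can stop for benefit on its primary outcome, yet alpha and power are those of a trial analysed once. The cited formulas are linked to the interim analysis only. Nothing says that the final test and its interval use what the interim looks leave. If the final test is run at 0.05 after efficacy looks, the overall error exceeds 5%. If strict control is kept, power is below that of the single-look calculation. How far depends on the boundary.

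Second, the interim and final statistics differ in what they estimate. The composite of severe events (death, heavy transfusion, intensive care, embolisation or operative intervention) occurs after randomisation and can be affected by treatment. Much of it is also a consequence of heavy blood loss. Adjusting the primary comparison for it can remove part of the effect under test or distort it. A boundary that is calibrated for the difference in proportions does not automatically hold for that adjusted statistic, and naming a boundary in a charter would not cure this.

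**Working it through.** **Inputs.** Sample size calculation: control rate "about 30% of all women will proceed from 500 ml to 1000 ml of blood loss", reduced to 15%; alpha 0.05; power 0.80; planned total 250. Randomization section: 1:1 allocation. Safety concerns: looks at 25, 75 and 125 per group, the last being the final analysis. Sidedness is not stated. Two-sided is assumed because it reproduces the printed number; a one-sided test gives 95 per arm.

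**1. Reproduce the printed sample size (one look, unpooled variance).**

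n = (1.960 + 0.842)² × [0.30 × 0.70 + 0.15 × 0.85] / 0.15² = 7.849 × 0.3375 / 0.0225 = 117.7, so 118 per arm.

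This matches, with no inflation for looks. The further 250 − 236 = 14 women are assigned to loss and incomplete data, so they are not an allowance for the looks.

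**2. Information fractions.** 25/125 = 0.2, 75/125 = 0.6, 125/125 = 1.

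**3. Overall two-sided error.** This integrates the joint normal distribution of the three statistics, treating a crossing on the primary outcome alone as a stop. The spending functions are:
- O'Brien-Fleming-type, 0.025 per side: α(t) = 4[1 − Φ(2.241/√t)]
- O'Brien-Fleming-type, applied to 0.05 as a whole: α(t) = 2[1 − Φ(1.960/√t)]
- Pocock-type: α(t) = 0.05 ln[1 + (e − 1)t]

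| Interim rule | Nominal p at looks 1, 2 and final if all looks are covered | Error if all looks are covered | Error if the final test stays at 0.05 |
|---|---|---|---|
| O'Brien-Fleming-type, 0.025 per side | 0.000001, 0.0076, 0.0476 | 5.0% | 5.2% |
| O'Brien-Fleming-type, 0.05 as a whole | 0.00001, 0.011, 0.046 | 5.0% | 5.4% |
| Pocock-type | 0.0148, 0.0238, 0.0236 | 5.0% | 7.2% |
| Every look at 0.05 | – | – | 5.0 + 3.8 + 2.7 = 11.5% |

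If the schedule is instead read as every 50 women in total (five looks), the 0.025-per-side O'Brien-Fleming-type and the Pocock-type rules with the final test at 0.05 give 5.7% and 7.4%. The worst case becomes 14.2%.

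**4. Power for 30% against 15%.** The drift is 0.15 / √(0.3375/n), which is 2.805 at n = 118 and 2.887 at n = 125.

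| Design | 118 per arm | 125 per arm |
|---|---|---|
| Single look | 80.1% | 82.3% |
| O'Brien-Fleming-type (both versions) | 79.5–79.8% | 81.7–82.0% |
| Pocock-type | 73.7% | 76.3% |

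With a pooled variance the figures are about one point lower: 78.8% and 81.1% for the 0.025-per-side version, 72.7% and 75.3% for Pocock-type.

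**5. The two analyses side by side.** Interim: the primary outcome corrected for risk factors and for the difference in the combined severe outcome. Final: difference in proportions, with regression only for large baseline imbalance. Risk factors precede randomisation; the severe outcome does not. The documents give no data from which to size the resulting distortion, so no figure is attached to it.

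**The case against.** The article does not leave the interim analysis uncontrolled. It cites formulas for it and points to a charter, and boundaries are commonly set out there or in an analysis plan. The missing numeric boundary is therefore no fault in itself. Stopping also needs lower morbidity as well as less progression, which is stricter than crossing on the primary outcome alone. Under O'Brien-Fleming-type bounds the whole issue amounts to a few tenths of a percentage point of error and less than one point of power. All of this stands.

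A reader might infer that the final test is fixed at 0.05, so that the true error is 11.5% or more. The documents do not support that. The figure 0.05 appears only as a sample-size input and could be the overall level. The final analysis has no stated level, and testing every look at 0.05 sits badly with the citation of interim formulas.

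A reader might also infer that no group-sequential boundary could apply because the interim analysis is adjusted. That goes too far. Covariate-adjusted statistics can be monitored, and the final analysis itself allows regression for baseline imbalance. The problem is narrower: the correction includes a post-randomisation outcome, and it is not the planned final statistic. The sentence on correction could be read more kindly, with the severe outcome as a second endpoint under analysis rather than a covariate. If that was meant, the text needs to say so.

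**Conclusion.** The point holds in a limited form. The article plans efficacy looks, sizes the trial for one look, ties no final level to alpha spent, and describes an interim analysis that does not target the effect of the final one. From the article, a 5% overall error and 80% power cannot be confirmed; neither is shown to be wrong.

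The overall error is exactly 5% if spending covers all looks. With the final test left at 0.05, it is 5.2–5.4% (O'Brien-Fleming-type) or about 7.2% (Pocock-type). The 11.5% is a ceiling for the three-look reading. Power at 118 per arm falls by less than one point under O'Brien-Fleming-type spending and by about six points (80.1 − 73.7 = 6.4) under Pocock-type.

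These figures assume a two-sided test, information proportional to the number of women, looks at 25/75/125 per group, no loss, and stopping on the primary outcome alone. The morbidity condition would lower the error figures. The charter may settle the boundary; it would not by itself settle the difference between the two statistics.

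**What to change.** - Use the difference in proportions of the final analysis as the monitoring statistic at every look. Keep interim results adjusted for risk factors as supportive, and drop the combined severe outcome from the adjustment.
- Before the final analysis, have the board record the boundary it applied in October 2017 and the number of women analysed, which the article does not give.
- Judge the final test at the level that remains, with a matching confidence interval. If O'Brien-Fleming-type spending with 0.025 per side was used at 50/150/250 women, the nominal p-values are about 0.000001, 0.0076 and 0.0476, and the interval is 1 − 0.0476, about 95.2%. If the function was applied to 0.05 as a whole, they are about 0.00001, 0.011 and 0.046, with an interval of about 95.4%. Recompute if the looks fell at other counts.
- Restate the sample-size paragraph: 0.05 as the overall two-sided level, 0.80 as power rather than beta, and power with the looks included (79.5–79.8% at 118 and 81.7–82.0% at 125 per arm, or about 74% and 76% if Pocock-type bounds were used).

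The cost is wording in the analysis section and the charter, a slightly stricter final level and slightly lower stated power, with no extra patients. If Pocock-type bounds were in fact applied, the cost is larger: a final level of about 0.024 and a visible loss of power, which should be reported as such.

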## Discussion

Postpartum hemorrhage is increasing in incidence in industrialized countries; there is no evidence-based managing protocol regarding fluid resuscitation. Volume resuscitation can be done with crystalloids, colloids, or red blood cells, which all have advantages and disadvantages. Resuscitation with crystalloid fluids means that large amounts are needed, which may induce acidosis and coagulopathy, the formation of interstitial edema and impairment of the microcirculation [15]. Colloid fluids, in particular synthetic colloids, such as hydroxyethyl starch solutions, may impair clot formation and therefore increase blood loss [16, 17]. Furthermore, even new-generation medium molecular weight hydroxyethyl starch solutions disturb fibrin polymerization in patients undergoing spine surgery [18]; the presence of hydroxyethyl starch solutions or gelatin solutions in patients with fibrinolysis leads to faster clot disintegration [19]. Once 30–40% of the circulating blood volume is lost, red blood cell replacement will be required. Red blood cells cannot be used for massive fluid therapy and one must be careful not to use uncrossmatched blood, especially in young fertile women, because of the possibility of irregular antibody formation and its effect on future pregnancies.

Restrictive or permissive resuscitation has recently been advocated as an alternative to the current standard care. In animal studies, military settings, and studies of non-pregnant trauma patients, controlled hypotensive resuscitation has been investigated. These studies have shown that there might be an advantage for a restrictive fluid resuscitation strategy. However, there are few well-performed randomized controlled trials. This might be due to ethical concerns in life-threatening conditions, but is nonetheless important to improve survival and morbidity, relying on evidence-based medicine. Until recently, high-volume fluid resuscitation strategies have been used to reverse hemorrhagic shock by replacing blood loss with intravenous fluid or transfusions. This strategy has been the gold standard, even though it has not been tested in prospective randomized clinical trials and has considerable limitations and risks. Increasing evidence has demonstrated that aggressive crystalloid-based resuscitation strategies are associated with cardiac and pulmonary complications, gastro-intestinal dysmotility, coagulation disorders, and immunological and inflammatory mediator dysfunction. Aggressive fluid administration increases arterial and venous pressures, but aggravates the dilution of clotting factors and blood viscosity, which results in increased hemorrhage volume, decreased oxygen delivery, and decreased survival rates [20]. Continued fluid administration and positive fluid balances have not been shown to improve renal outcomes and may worsen overall prognosis in acute kidney failure [21]. Also, maintaining a high or “normal” blood pressure in patients with uncontrolled hemorrhagic shock can result in the “lethal triad” of hypothermia, acidemia, and coagulopathy [22].

Theoretical concerns regarding the safety of restrictive resuscitation are based on the possible harmful effects of decreased oxygen delivery to the various tissues of the body due to shock. Maintaining a blood pressure that is too low could potentially result in inadequate perfusion and subsequent organ failure. Intraoperative restrictive resuscitation has been successfully used in several animal models [23]. The results of Lu *et al.* [24] showed that aggressive fluid resuscitation to restore near-normal mean arterial pressure of 80 mmHg during uncontrolled hemorrhage induced massive blood loss and excessive hemodilution. Controlled fluid resuscitation to maintain mean arterial pressure of 40 mmHg in the presurgical treatment of severe and uncontrolled hemorrhagic shock decreased further blood loss, avoided excessive hemodilution and coagulopathy, improved the early survival rate, and reduced apoptosis of the visceral organs [24].

Two randomized controlled trials investigated restrictive resuscitation protocols in trauma patients. The preliminary results on 90 patients in a randomized controlled trial conducted by Morrison *et al.* [25] showed fewer early postoperative deaths and significantly fewer blood product transfusions in the study group, without differences in the incidence or severity of coagulopathy, thrombocytopenia, or anemia. In this study, the difference in mean arterial pressure between both study groups was not statistically significant and the actual mean arterial pressures for the two groups were much more similar than might be expected based on the target goals for resuscitation [25]. The final results of this trial, including results obtained with the targeted 271 patients, have not been published yet. Dutton *et al.* [26] found no significant difference in mortality between the study groups in a trial in which maintaining a systolic blood pressure > 100 mmHg was compared with targeting a systolic blood pressure of 70 mmHg [26]. One of the limitations of this study is that no power analysis was performed before initiating the study and determining the sample size (*n* = 110) Also, as in the previously mentioned study, the proposed target blood pressure in the study group was not achieved.

A retrospective analysis by Duke *et al.* [27] of trauma patients showed an overall lower mortality rate, lower intraoperative mortality, and a shorter hospital stay in the restrictive resuscitation group. Despite the fact that the groups were well-matched, the retrospective character of the study is a limitation and bias cannot be ruled out [27].

A prospective randomized pilot trial comparing controlled resuscitation versus standard resuscitation in hypotensive trauma patients demonstrated that controlled resuscitation strategy can be successfully and safely implemented in a civilian environment. The results showed a reduction of early crystalloid resuscitation volume, but also an increase in early blood product transfusion [28].

In all, these studies, there were difficulties in following the study protocol strictly. This may be explained by the fact that these studies were performed in an acute setting and by the impossibility of blinding the treating clinicians, who might be less familiar with restrictive resuscitation.

In conclusion, there is little and contradictive evidence for either aggressive or restrictive fluid resuscitation, and it is very difficult to perform good clinical trials. This is reflected in the latest guidelines. The European Society of Anaesthesiology guidelines on management of severe perioperative bleeding recommend avoidance of hypervolemia. Permissive hypotension is not mentioned, but implementation of delayed or low-volume resuscitation protocols is not yet recommended [29]. Conversely, the updated European guidelines on management of bleeding and coagulopathy following major trauma recommend a target systolic blood pressure of 80 to 90 mmHg until major bleeding has been stopped in the initial phase following trauma without brain injury [30].

All these results, mainly obtained for trauma patients, cannot be extrapolated to pregnant women during labor, in view of the physiological hemodynamic and hemostatic changes that occur in pregnancy [31, 32]. Plasma volume increases up to 40% during pregnancy, whereas red blood cell count only increases by 30%, cardiac output is increased, and systolic and diastolic blood pressure decrease slightly in the second trimester and elevate toward term pregnancy. At the end of normal pregnancy, changes in the coagulation and fibrinolytic system result in an apparent hypercoagulable state [33–35] to minimize blood loss at delivery. In patients with PPH, this equilibrium will be altered and may lead to profound and rapid changes in hemostasis. In some cases, the disruption of the coagulation precedes delivery and may contribute significantly to development of PPH [36]. Timely recognition and prompt intervention are crucial for the successful management of PPH [37]. In non-pregnant individuals with massive blood loss, restrictive fluid management has been shown to prevent a progression to dilution coagulopathy [16–19].

In conducting this study, we hope to find the best managing option for treating PPH and to achieve a decrease in adverse outcomes by reducing the severity of PPH.

## Trial status

Protocol version 8, February 2015. Recruitment started August 2014. The trial is ongoing; 179 out of the 250 patients have been enrolled in the study. A planned interim analysis in October 2017 by the data safety monitoring board showed no safety issues needing discontinuation and a high likelihood that the hypothesis will be proven. The trial will end if the 250 patients are reached or when the data safety monitoring board intervenes after planned interim analysis.

## Abbreviations

NVOG: Nederlandse Vereniging voor Obstetrie en Gynaecologie
PPH: postpartum hemorrhage
REFILL: Restrictive Versus Massive Fluid Resuscitation Strategy
TIDieR: template for intervention description and replication
